## Methods

2.

This study was approved by the local ethics committee of Sao Paulo State University (approval number: 4.6549.629). All participants provided written informed consent. Baseline assessments have already been performed, and participants are currently being followed up.

### Participants

2.1.

Participants aged 18 to 40 years were recruited through advertisements at social media, universities, gyms and public parks and divided in two groups: individuals with PFP (*n* = 144) and control individuals without PFP (*n* = 85). The following inclusion criteria were considered for PFP group (29): (i) Insidious symptoms of PFP lasting at least three months, (ii) worst knee pain in the last month of at least 20 mm on a 0–100 mm Visual Analogue Pain Scale (VAS), (iii) symptoms of PFP during activities that load patellofemoral joint (e.g., squatting, running, jumping, prolonged sitting, stair negotiation). To be included in the control group, participants had no signs or symptoms of PFP or other neurological or lower limb musculoskeletal conditions. Exclusion criteria for both groups were history of: patellar subluxation, surgery in any lower limb joint, trauma or injury at the knee, or ligament instability. Additional exclusion criteria for the follow-up assessments are: (i) occurrence of knee trauma or injury (both groups); (ii) development of knee pain (only for control group); (iii) development of other medical conditions that may influence the findings (both groups). Participants’ baseline demographics are presented in Table 1.

**Table 1 T1:** Participants’ demographics at baseline.

Variables	PFP group (*n* = 144) Mean ± SD	Control group (*n* = 85) Mean ± SD
Females (*n*)	108	64
Males (*n*)	36	21
Age (years)	23 ± 5	22 ± 3
Height (cm)	166 ± 8	165 ± 9
Body mass (kg)	68 ± 14	62 ± 13
BMI (kg/cm^2^)	25 ± 4	23 ± 4

Abbreviations: SD, standard deviation; PFP, patellofemoral pain; BMI, body mass index.

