## Introduction

1.

Patellofemoral pain (PFP) is characterized by an insidious onset of pain at the anterior/peri/retropatellar region of the knee (1). Its prevalence is approximately 25% in the general population and 35% in professional athletes (2). Disability, reduced physical activity, and impaired social life are reported in those with PFP (3, 4). Other impairments such as lower self-reported function, physical performance, and health-related quality of life (HRQOL) have also been reported in individuals with PFP, alongside with a possible progression to osteoarthritis (5–8).

PFP is multifactorial and involves a number of physical (e.g., kinetics, kinematics, muscle function) and non-physical features (e.g., psychological or lifestyle factors) (9–11). Proximal, local, and distal kinematics, kinetics, and muscle function impairments have been reported in those with PFP (1, 9, 12–17), and linked with increases in patellofemoral joint (PFJ) load during various tasks (9), a factor suggested to play a central role in PFP (9). Beyond this pathomechanical model of PFP (8), there is an increased awareness that non-physical features may be important in understanding PFP (18). Pain processing (e.g., local and central sensitization) and psychological features (e.g., kinesiophobia and pain catastrophizing) have also been reported to be altered in individuals with PFP (10, 11). Both physical and non-physical features are associated with worse pain, function, and disability (19–22). Some associations among physical and non-physical features with PFP are still not clear, including their prospective association in the long-term. The prospective association of PFJ load with PFP has also not been investigated, despite its proposed critical role (9).

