PFP is not self-limiting and is challenging to manage, with symptoms persisting for nearly two decades. Long-term pain is reported to continue in one of every two patients even after treatment (3, 23). Symptom severity may remain unchanged or increase in 50% of affected individuals (24, 25). As such, a similar prospective pattern would also be expected for physical and non-physical features given their previously reported cross-sectional association with PFP. Symptoms duration of individuals with PFP has been previously associated with biomechanical (26) and muscle function parameters (27), as well as pain itself (27, 28). However, the majority of the studies conducted to date have a cross-sectional or interventional design, which precludes the understanding of the natural history of these features in individuals with PFP.

Understanding changes over time in physical and non-physical features in individuals with PFP is a first step to gain knowledge regarding their evolution as part of PFP and its progression. In addition, investigating the prospective association of clinical outcomes (i.e., self-reported pain, physical performance measures, self-reported function, HRQOL and physical activity level) with physical and non-physical features may contribute to the identification of predictors of pain and disability in the long-term, as well as possible targets for interventions.

We have, therefore, designed a prospective longitudinal study aiming to investigate group-by-time changes over a minimum of 15 months in individuals with PFP, measuring their biomechanical, muscle function, pain processing, psychological features and clinical outcomes. In addition, we aim to investigate the extent to which changes in biomechanical, muscle function, pain processing, and psychological features are associated with changes in clinical outcomes. We hypothesize that: (1) individuals with PFP will present worse biomechanical, muscle function, pain processing, psychological features, and clinical outcomes at follow-up as compared to baseline; (2) potential differences in outcomes as compared to asymptomatic individuals at baseline will increase at follow-up; (3) changes over the time in biomechanical, muscle function, pain processing, and psychological features will be associated with changes in clinical outcomes; (4) there will be an association between changes over the time in biomechanical and psychological features.

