### Statistical analysis

2.10.

Descriptive statistics (mean, median, standard deviation, and interquartile intervals) will be calculated for all variables of interest. Generalized Linear Mixed Model (GLMM) will be used to investigate group-by-time differences. The type of matrix will be chosen according to the Akaike Information Criterion (AIC) in order to assess the adherence index of the model (56). The lower the AIC, the higher the adherence (56). Group and time interaction effects will be considered fixed, while participant effects will be considered random. Pairwise comparisons will be performed with Bonferroni *post hoc* tests when significant interactions or main effects are determined. Mean differences [95% confidence intervals (CI)] and effect sizes (Cohen’s *d* [95% CI]) for each *post hoc* comparison will be calculated. The guidelines for interpreting the Cohen’s *d* are: 0 to 0.40 small effect, 0.41 to 0.70 moderate effect, 0.71 or large effect (57). Statistical significance level will be set at .05.

For the first stage of the regression analyses, univariate linear regression models will be used to determine to what extent changes in each biomechanical, muscle function, pain processing and psychological features are associated with changes in self-reported pain, physical performance measures, self-reported function, HRQOL and physical activity level in individuals with PFP. A significance level of *p* ≤ .10 rather than the conventional level of *p* < .05 will be used to ensure that the univariate analyses are sufficiently sensitive to identify potential prognostic factors for entry in the model (58). For the second stage, all potential prognostic factors that showed significant associations on univariate analyses will be entered into a stepwise multivariate linear regression with backward elimination (*p* ≤ .10) in order to identify a group of factors that are independently associated with the clinical outcomes. For the final multivariate models, the significance will be set at .01 to minimize the results being adversely influenced by the likelihood of increased risk of Type I error associated with multiple analyses. The predictive power of each final model will be determined by calculation of the percentage of explained variance (adjusted *R*^2^).

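### Controls who develop knee pain are excluded from follow-up, so the comparator for the group-by-time contrast is selected on a post-baseline outcome

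*Protocol article*

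**What the plan says.** The Participants section (2.1) describes two groups at baseline: "individuals with PFP (*n* = 144) and control individuals without PFP (*n* = 85". At entry, PFP participants needed "worst knee pain in the last month of at least 20 mm on a 0–100 mm Visual Analogue Pain Scale (VAS". For the control group, "participants had no signs or symptoms of PFP or other neurological or lower limb musculoskeletal conditions".

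The same section then sets rules that act after baseline. The first is "Additional exclusion criteria for the follow-up assessments are: (i) occurrence of knee trauma or injury (both groups". The next two are "ii) development of knee pain (only for control group); (iii) development of other medical conditions that may influence the findings (both groups". The knee-pain rule is the only one of the three confined to one group.

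The first aim is group-by-time change. Hypothesis 2 in the Introduction states that "potential differences in outcomes as compared to asymptomatic individuals at baseline will increase at follow-up". In Statistical analysis (2.10), a generalized linear mixed model with a random participant effect "will be used to investigate group-by-time differences", tested at .05. That section describes no analysis that retains or accounts for controls removed under the knee-pain rule, and the limitations in the Discussion do not mention the selection.

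**The concern.** Group membership is fixed at baseline, but whether a control contributes follow-up data depends on what happens afterwards. The event that removes a control is knee pain, which is measured as an outcome and is expected to move with the other features under study. The controls who remain are those who stayed well.

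If controls who develop pain also worsen on strength, movement, pain processing or psychological scores, dropping them makes the control group's average course look better than that of the cohort enrolled. The PFP-minus-control difference in change then moves toward the widening that hypothesis 2 predicts, even when the two groups follow the same course. Follow-up is already running, so a control turned away now is information that no later analysis can recover.

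**Working it through.** The article gives no power, effect-size or incidence figure for this contrast, so there is nothing to reproduce. The size has to be worked out under stated assumptions.

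**Inputs from the article.** 144 PFP and 85 control participants; significance level .05 (sidedness not stated, two-sided assumed); for VAS, an SEM of 6 mm and an MCID of 20 mm (Self-reported pain).

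**Assumptions.**
- q, the share of controls who develop knee pain: 5% to 25%.
- D, how much worse those controls change than the others: 0.5 SD of change for a general feature.
- Mean worst pain of 20 to 40 mm in those controls, with no VAS change in pain-free controls.
- No losses other than this exclusion.

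**Step 1: bias.** Let m be the mean change in controls who stay pain free. The mean over all controls is (1 − q)m + q(m + D) = m + qD. After the exclusion it is m. The contrast therefore shifts by qD toward widening.

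**Step 2: type I error with no true difference in change.** SE = √(1/144 + 1/(85(1 − q))), and P(reject) = Φ(qD/SE − 1.96) + Φ(−qD/SE − 1.96).

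| q | Controls kept | Bias, D = 0.5 SD | P(reject) | VAS shift, 20–40 mm |
|---|---|---|---|---|
| 5% | about 81 | 0.025 SD | 0.054 | 1–2 mm |
| 10% | about 76 | 0.050 SD | 0.064 | 2–4 mm |
| 20% | 68 | 0.100 SD | 0.104 | 4–8 mm |
| 25% | about 64 | 0.125 SD | 0.132 | 5–10 mm |

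At q = 25%, for example, SE = √(1/144 + 1/63.75) = 0.150 and 0.125/0.150 = 0.83, giving 0.132. The result is sensitive to D: at D = 1.0 SD, P(reject) runs from 0.065 (q = 5%) to 0.383 (q = 25%).

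**Step 3: does the mixed model repair it?** A likelihood-based mixed model can use the baseline values of participants without follow-up, and is valid if missingness depends only on observed data. Here it depends on knee pain at follow-up. This was simulated with 3,000 replicates per setting, no true group-by-time effect, pain liability correlated 0.5 with the follow-up outcome, and baseline-to-follow-up correlation of 0.5 or 0.7. Over q = 5–25%, in SD of the outcome:
- all controls followed: within 0.004 of zero;
- retained controls only: shift of 0.02 to 0.11 toward widening;
- excluded controls' baselines kept, with follow-up predicted from the retained controls (a stand-in for a missing-at-random mixed model): shift of 0.03 to 0.17.

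Keeping the baselines does not help. In the retained-only analysis, selection at baseline partly cancels selection at follow-up; restoring the baselines removes that cancellation.

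**Step 4: which analyses use the controls.** Hypothesis 1 concerns change within the PFP group, and the regressions of change are specified for PFP participants. Neither uses control data. The distortion is confined to the group-by-time contrast.

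**The case against.** The best defence is that the intended comparator is people who stay asymptomatic. Hypothesis 2 refers to asymptomatic individuals and controls are defined by absence of symptoms, so removing those who become symptomatic preserves the reference state. This has some force, but the article never defines the comparator that way, and the wording of hypothesis 2 can equally mean people asymptomatic at baseline. Staying well for 15 months or more cannot be known at enrolment, so that contrast does not describe the course of a pain-free cohort. A labelled sensitivity analysis serves that reading fully.

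The second defence is size. The article's only related figure, "Its prevalence is approximately 25% in the general population", is a prevalence of PFP, not an incidence of knee pain in screened, pain-free adults, and it supports no particular q. The values of D are assumptions too. At 5% and 0.5 SD the effect is negligible. This stands, and it limits how strongly the point can be put.

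Three stronger readings are tempting, and the documents do not support them:
- **That the fault is asymmetry, because PFP participants who recover are kept.** No rule removes them, and keeping them is correct for a natural-history question. Removing them would add to the bias.
- **That the rule is bound to produce a widening gap in pain.** PFP participants entered with worst pain of at least 20 mm, so regression to the mean pulls their VAS down and narrows the gap. The net direction for VAS is not fixed.
- **That the criterion on other medical conditions is a parallel defect.** It is loosely worded, but it applies to both groups, and a condensed article may leave its operation to the full protocol.

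**Conclusion.** The concern holds for one contrast. The control-only exclusion conditions the comparator on a post-baseline outcome, adds a bias toward the hypothesised widening, and is not corrected by the planned model. With 5–25% of controls affected and a 0.5 SD worse change, the bias is about 0.025–0.125 SD and type I error about 0.054–0.13 per outcome. The VAS shift of 1–10 mm compares with an MCID of 20 mm. The direction of this component is clear if affected controls worsen; its size rests on an incidence and a severity that the article does not give.

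A reader might infer that the study's findings as a whole are compromised. They are not: within-PFP change and the regressions in PFP participants do not depend on controls. The VAS contrast also has a limit of its own, since controls start near the floor whatever the follow-up rule. This should be fixed, but it does not invalidate the design.

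**What to change.** - Remove the knee-pain criterion for controls as a follow-up exclusion. Assess every returning control whatever their knee pain, and analyse by baseline group in the main mixed model.
- Report how many controls developed knee pain. Give the comparison with persistently pain-free controls as a labelled sensitivity analysis.
- If any controls have already been declined, report their number and the reasons, and add a sensitivity analysis that allows data to be missing not at random. A change of wording cannot recover those visits.
- For VAS, base the conclusion on change within the PFP group rather than on the interaction.

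The cost is an amendment, a few more visits among people already due to be contacted, and somewhat more heterogeneous control data.

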### Procedures

2.2.

Follow-up assessments will be performed in two separate days, identically to the baseline (Figure 1). In the first day, characteristics of the participants, self-reported measures, Pressure Pain Thresholds (PPTs), physical performance measures, anterior and lateral trunk endurance, 3D kinematics and kinetics will be assessed. Participants will be oriented to perform all tasks barefoot and wear light clothes. In the second day, maximal torque, rate of torque development (RTD), and force steadiness of the hip abductors and knee extensors/flexors will be assessed. Physical performance measures and lateral trunk endurance will be assessed bilaterally, while PPTs, 3D kinematics and kinetics, and muscle function measures will be assessed in the symptomatic or most symptomatic knee (bilateral symptoms) in individuals with PFP. For controls, the assessed limb will be randomly selected. The same limb assessed in the baseline will be collected in the follow-up. At least 15 months after the baseline assessment, participants will be contacted by phone or e-mail and invited to return to the follow-up assessment.

**Figure 1 F1:**
[figure not shown]
Flowchart depicting the experimental design of the study.

### Characteristics of the participants and self-reported measures

2.3.

Age, pain laterality, and duration of PFP symptoms in months will be initially obtained. Weight and height will be assessed using a calibrated scale with a stadiometer (WELMY 110; WELMY, Brazil). Knee and ankle width will be measured using a pachymeter (150 mm × 0.05 mm/6”X1/128”; MARBERG, China) and lower limb length will be measured with a measuring tape from the anterior superior iliac spine to the medial malleolus. The anthropometric measures will be posteriorly included in the biomechanical model. Percentages of body fat and skeletal muscle mass will be assessed using a bioelectrical impedance analyzer (OMRON HBF 514C; OMRON Healthcare; Japan) and calculated with valid and reliable equations provided by the manufacturer (30). Subscapular, triceps, biceps and suprailiac skinfolds will be measured with a caliper (CESCORF TOP TEC; CESCORF, Brazil) following the recommendations of the International Standards for Anthropometric Assessment (31). The measures will be obtained along the right side of the body for 3 consecutive times, and the mean will be used for statistical analysis. Afterwards, participants will answer self-administered scales and questionnaires translated and cross-culturally adapted for the Brazilian population, which are detailed below (32–36).

#### Self-reported pain

2.3.1.

The self-reported knee pain will be assessed with the 0–100 mm VAS, where 0 represents no pain and 100 the worst pain imaginable. The worst level of pain during the last month, and the current level of pain (at the beginning of data collection) will be obtained. Participants will be also asked about their level of pain after biomechanical assessment and muscle function assessment. The VAS has been previously validated for individuals with PFP and has good reliability (intraclass correlation coeficient [ICC] = .76; standard error of measurement [SEM] = 6 mm; minimal clinically important difference [MCID] = 20 mm) (37).

#### Self-reported function

2.3.2.

Self-reported function will be assessed using the Anterior Knee Pain Scale (AKPS). The AKPS is a 13-item questionnaire that evaluates subjective symptoms and functional limitations in patellofemoral disorders (e.g., atrophy, subluxation, pain, swelling, difficulty performing daily activities). It has been validated for individuals with PFP and has good reliability (ICC = .81; SEM = 3.1 points; MCID = 10 points) (37, 38). The maximum score for each item ranges from 5 to 10, and the sum of all items generates a score ranging from 0 (maximal disability) to 100 (no disability).

#### Kinesiophobia

2.3.3.

Kinesiophobia will be assessed using the TAMPA Scale for Kinesiophobia (TSK). This is a valid and reliable tool developed to measure fear of painful movement or (re)injury (ICC = .82; SEM = 3.16 points; [MCID] = 4 points) (33, 39). The questionnaire consists of 17 items with statements related to fear of movement or (re)injury and participants are instructed to respond how much they agree with each of them, with ratings ranging from “strongly agree” to “strongly disagree”. The score of each item ranges from 1 to 4, and the sum of all items generates a final score ranging from 17 to 68, with higher scores representing higher kinesiophobia.

#### Pain catastrophizing

2.3.4.

Pain catastrophizing will be assessed using the Pain Catastrophizing Scale (PCS). This is a valid and reliable tool that assesses the excessively negative orientation towards actual or perceived pain (ICC = .90; SEM = 2.79 points; minimal detectable change [MDC] = 7.73 points) (34, 40). The questionnaire consists of 13 items with statements related to catastrophizing and participants are instructed to respond to what degree they describe their thoughts or feelings at the time of pain, with ratings ranging from “not at all” to “all the time”. The score of each item ranges from 0 to 4, and the sum of all items generates a final score ranging from 0 to 52, with higher scores representing higher pain catastrophizing.

#### Health-related quality of life

2.3.5.

The Medical Outcome Short-Form 36 (SF-36) will be used to assess HRQOL. This tool has been previously validated, and has satisfactory intra-rater reliability (*r* = .44 to.84) (41, 42). The SF-36 is composed of general questions related to eight domains: physical functioning, role physical, bodily pain, general healthy, vitality, social functioning, role-emotional and mental health. The questions result in a score for each domain ranging from 0 to 100, with higher scores representing better HRQOL. The eight domains will be summarized in the mental and physical components that will be calculated as per Taft et al. (43).

#### Physical activity level

2.3.6.

Self-reported physical activity level will be assessed using the Baecke's Habitual Physical Activity Questionnaire. This is a valid and reliable questionnaire (ICC = .92). The questionnaire consists of 16 questions related to type, duration and intensity of physical activities performed by the participants in the last 12 months. The questions result in three scores that represents three domains: physical activity at work, leisure practices and occupation of free time, and locomotion which range from 1 to 5 (44). Higher scores indicate higher levels of physical activity.

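### For PFP participants with under 12 months of symptoms, the baseline Baecke score includes pre-onset months and the follow-up score does not, so their activity change may be biased toward decline

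*Protocol article*

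**What the plan says.** - **Entry (section 2.1).** The PFP group needs "Insidious symptoms of PFP lasting at least three months". No upper limit is set.
- **Instrument (section 2.3.6).** The Baecke questionnaire asks about the type, "duration and intensity of physical activities performed by the participants in the last 12 months". It gives three domain scores, each from 1 to 5, with higher meaning more active.
- **Timing (section 2.2).** "At least 15 months after the baseline assessment, participants will be contacted by phone or e-mail". The same instrument is used at both visits: "Follow-up assessments will be performed in two separate days, identically to the baseline".
- **Role of the outcome (Introduction).** The clinical outcomes are "self-reported pain, physical performance measures, self-reported function, HRQOL and physical activity level". Hypothesis 1 expects the PFP group to have worse "psychological features, and clinical outcomes at follow-up as compared to baseline". Hypothesis 2 expects baseline differences from asymptomatic individuals to grow.
- **Background premise (Introduction).** "Disability, reduced physical activity, and impaired social life are reported in those with PFP".
- **Data available (section 2.3).** "Age, pain laterality, and duration of PFP symptoms in months will be initially obtained". Table 1 does not report the distribution of duration.
- **Analysis (section 2.10).** The mixed model has fixed group and time effects with their interaction, and a random participant effect. The regressions relate changes in features to changes in outcomes within the PFP group. Symptom duration is not used in either. The limitations paragraph in section 3 does not mention the recall window.

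**The concern.** A change score should compare the same person in the same kind of period at two times. For a participant whose PFP began less than 12 months before enrolment, the two Baecke scores do not do this. The first mixes months without PFP and months with it, and the second covers only months after onset. Part of the difference can then reflect the onset of PFP, which happened before enrolment, and not its course during follow-up. The study sets out to describe that course.

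The control group does not cancel the effect, because controls have no onset inside their baseline window. If activity is lower after onset, the artefact works in favour of hypothesis 1 (decline in PFP) and hypothesis 2 (a widening gap to controls). Within the PFP group, the activity-change outcome also gains a component that depends on how recently symptoms began.

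**Working it through.** The article states no figure on this point, so there is none to reproduce. The check is window arithmetic followed by illustrations whose inputs are labelled.

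**Inputs from the article.** Minimum duration 3 months (2.1); recall window 12 months (2.3.6); interval between visits at least 15 months (2.2); domain scores 1 to 5 (2.3.6).

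**Step 1. Pre-onset time in the baseline window.** Months before onset = max(0, 12 − d), where d is symptom duration in months. The share is f = max(0, 12 − d)/12.

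| d (months) | pre-onset months | share f |
|---|---|---|
| 3 | 9 | 75% |
| 6 | 6 | 50% |
| 9 | 3 | 25% |
| 12 or more | 0 | 0% |

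**Step 2. Pre-onset time in the follow-up window.** At 15 months the window runs from month 15 − 12 = 3 to month 15 after baseline; at 24 months, from month 12 to month 24. In every case it starts after baseline and so after onset. Pre-onset months: 0. The two windows do not overlap.

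**Step 3. Bias for one participant.** Assume the score averages evenly over its window, and that activity falls by D points after onset and then stays constant. True change during follow-up is 0, but measured change is −f × D. At d = 3 this is −0.75D, or −0.19, −0.38 and −0.75 points for assumed D of 0.25, 0.5 and 1.0.

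**Step 4. Bias in the PFP group mean.** Let p be the proportion with under 12 months of symptoms. Bias = −p × (mean f among them) × D. The largest value has all of them at 3 months (mean f = 0.75). If durations are spread evenly from 3 to 12 months, mean f = 4.5/12 = 0.375. With assumed D = 0.5:

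| p (assumed) | all at 3 months | even over 3–12 months |
|---|---|---|
| 10% | −0.04 | −0.02 |
| 25% | −0.09 | −0.05 |
| 50% | −0.19 | −0.09 |

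**Step 5. A second assumed shape.** Take log-normal durations with log SD 1, cut at 3 months, by numerical integration:

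| median before the cut (months) | share under 12 months | bias in group mean | bias among those under 12 months |
|---|---|---|---|
| 12 | 45% | 18% of D | 41% of D |
| 24 | 23% | 8% of D | 35% of D |
| 36 | 13% | 4% of D | 32% of D |

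With D = 0.5 the group-mean bias is 0.09, 0.04 and 0.02 points, within the range of step 4.

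**Step 6. The change regressions.** The artefact is −f × D in the outcome, and f depends only on d. It adds scatter to the activity-change outcome in every case. It biases a coefficient only if d is correlated with change in that feature. The Introduction reports associations of duration with biomechanics, muscle function and pain, but not with their change.

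**The case against.** Several objections stand in whole or in part.

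- **Direction.** It rests on one background sentence, which says reduced activity is reported in people who have PFP. That is not a within-person fall and gives no timing. Onset is described as insidious, so a sharp before-and-after contrast is a simplification. This stands: the direction must be conditional.
- **Size.** Neither the duration distribution nor the fall after onset is given, and even averaging over the window is assumed; if respondents weight recent months more, the artefact shrinks. The Introduction describes symptoms lasting nearly two decades, which points toward few recent cases without proving it. This stands: the group-level effect may be small.
- **Scope.** One questionnaire among many outcomes is affected, and only in participants with under 12 months of symptoms. The recall window belongs to an established instrument. True, but the change in this outcome is hypothesised and modelled, so its meaning matters.
- **Omission.** A condensed article may leave a sensitivity analysis to a fuller plan. This explains the missing analysis. It does not remove the mismatch, which follows from the entry criterion, instrument and interval that the article itself fixes.

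A reader might infer that the planned activity results, including the regressions, are biased toward decline as a matter of course. The article does not support that. It shows that the two windows differ for recent cases, but not that activity fell at onset in these participants, how many are recent cases, or that duration is related to change in the features.

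**Conclusion.** The mismatch is real and follows from sections 2.1, 2.2 and 2.3.6 alone: up to 9 of 12 baseline months can precede onset, against none at follow-up, and neither the controls nor the models in 2.10 deal with it. If activity falls after onset, the measured Baecke change in participants with under 12 months of symptoms is biased toward decline, by up to 75% of that fall at a duration of 3 months.

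For the group mean and the group-by-time contrast the size is unknown. Under the illustrations with D = 0.5 it runs from about 0.02 to 0.19 points, and it could be smaller. These figures rest on an assumed fall, assumed shares or shapes of duration, and even averaging over the recall window. In the change regressions the certain cost is noise; bias needs a correlation between duration and change in the features. This is an inexpensive improvement to the analysis of one outcome and leaves the study's other results untouched.

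**What to change.** In section 2.10, for the Baecke outcome only, keep the all-participants analysis and prespecify beside it a sensitivity analysis limited, in the PFP group, to those with at least 12 months of symptoms at baseline. Apply it to the within-PFP change, the group-by-time contrast and the activity-change regressions.

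Alternatively, keep all participants and use max(0, 12 − duration)/12 for the PFP group, set to 0 for controls. In the mixed model it must enter as an interaction with time: as a main effect alone it shifts both visits equally and leaves the time and group-by-time contrasts uncorrected. In the change regressions it enters as a covariate. State that this term cannot separate the recall artefact from truly different change early in the course of PFP, because both depend on duration.

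Add a rule of interpretation: a fall in Baecke score that appears only among those under 12 months is not read as change during follow-up. Reporting the baseline distribution of symptom duration would show how far the issue reaches.

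**Cost.** No new data, since duration in months is already recorded. The restricted analysis has fewer PFP participants, wider intervals and a narrower population, which is why it stands beside the main analysis and does not replace it. It should be fixed before the follow-up data are analysed.
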